## Abstract

**Background:**

Prostate cancer is the most common male cancer in the Western world. The most substantial long term morbidity from this cancer is sexual dysfunction with consequent adverse changes in couple and intimate relationships. Research to date has not identified an effective way to improve sexual and psychosocial adjustment for both men with prostate cancer and their partners. As well, the efficacy and cost effectiveness of peer counselling as opposed to professional models of service delivery has not yet been empirically tested. This paper presents the design of a three arm randomised controlled trial (peer vs. nurse counselling vs. usual care) that will evaluate the efficacy of two couples-based sexuality interventions (ProsCan for Couples: Peer support vs. nurse counselling) on men's and women's sexual and psychosocial adjustment after surgical treatment for localised prostate cancer; in addition to cost-effectiveness.

**Methods/design:**

Seventy couples per condition (210 couples in total) will be recruited after diagnosis and before treatment through urology private practices and hospital outpatient clinics and randomised to (1) usual care; (2) eight sessions of peer-delivered telephone support with DVD education; and (3) eight sessions of oncology nurse-delivered telephone counselling with DVD education. Two intervention sessions will be delivered before surgery and six over the six months post-surgery. The intervention will utilise a cognitive behavioural approach along with couple relationship education focussed on relationship enhancement and helping the couple to conjointly manage the stresses of cancer diagnosis and treatment. Participants will be assessed at baseline (before surgery) and 3, 6 and 12 months post-surgery. Outcome measures include: sexual adjustment; unmet sexuality supportive care needs; attitudes to sexual help seeking; psychological adjustment; benefit finding and quality of life.

**Discussion:**

The study will provide recommendations about the efficacy of peer support vs. nurse counselling to facilitate better sexual and couple adjustment after prostate cancer as well as recommendations on whether the interventions represent efficient health service delivery.

**Trial Registration:**

ACTRN12608000358347

## Background

### The context of prostate cancer

Prostate cancer is the most common male cancer and second most common cause of cancer death in men in the Western world (excluding non melanoma skin cancer). In Australia, 1 in 11 men will be diagnosed with prostate cancer in their lifetime (0–74 years) and 1 in 82 will die from the disease [1]. In 2003 there were 13,526 Australian men diagnosed with prostate cancer with this number expected to increase to over 18,000 for 2006 [2]. Improved survival from prostate cancer has been demonstrated worldwide [3]. Around half of all newly diagnosed men are predicted to be alive 15 years after diagnosis [3] such that the large cohort of men living with the consequences of diagnosis and treatment is increasing.

The most frequently received treatment for prostate cancer in Australia is radical prostatectomy and the predominance of radical prostatectomy as the primary treatment approach for this cancer is mirrored elsewhere such as in North America [4,5]. While sexual dysfunction after all treatment approaches is common, the trajectory of this dysfunction and severity varies by treatment modality [6]. Men treated with radiation therapy experience less erectile dysfunction (ED) initially following treatment however, in contrast to radical prostatectomy, function is more likely decline over time. In addition, many men now receive neo-adjuvant hormone therapy with radiotherapy, further complicating the course of their sexual adjustment. For radical prostatectomy early adjuvant hormone therapy is uncommon and ED will be immediate due to surgical damage to the neurovascular bundle that lies adjacent to the prostate, with some improvement over the two years after surgery [7]. However, even with nerve sparing surgical techniques that aim to reduce damage to erectile function as few as 18.5% of men report being able to achieve erections firm enough for sexual intercourse two years after surgery [6,7]. Compared with their age mates, men with prostate cancer have a 10 to 15 fold increase in ED [8]. Other distressing effects of treatment include: penile shortening (68% of men), loss of sexual desire (60–80%), less satisfying orgasms (64–87%), overall sexual dissatisfaction (61–91%) [9,10]. These effects can lead to: impaired sexual performance; changes in relationships with women and sexual partners; lost enjoyment of sexual imaginings; decrements in masculine self esteem [10,11]. Problematically, many men are reluctant to seek help for sexual difficulties, with only about half of men seeking medical treatment for ED up to five years after treatment [10]. Reluctance to seek help is particularly problematic for men who receive radical prostatectomy as, for these men, an early return to sexual activity (by three months after surgery) may increase the recovery rate of spontaneous erections and improve responses to ED treatments [12]. Thus, support services for men with prostate cancer that are targeted to sexuality concerns need to reach men who receive radical prostatectomy within weeks of their cancer treatment.

Sexual dysfunction is a shared problem within couples, with regret and loss common among both members of the couple [13]. However, existing medical and support services for men with prostate cancer are oriented towards the patient, do not pay sufficient attention to the couple relationship and virtually ignore the needs of female partners of these men. Partners are more likely to focus on building their husband's self-esteem and putting the sexual dysfunction into perspective within the relationship, and less likely to focus on their own sexual needs [14]. Partners' quality of life is related to their reports of sexual function within the relationship and sexual dysfunction has implications for the longer-term psychosocial well-being of partners [15]. Women often are less focused on finding 'mechanical' treatments to regain erectile function and more open to counseling that might assist the couple to experience intimacy and closeness even if intercourse is not possible [16]. The attention to improving erectile rigidity in the man, for which 'mechanical' treatments are usually needed, may overshadow the partner's needs for sexual pleasure and stimulation [17].

The psychological distress of female partners is increased if they have limited knowledge of what to expect during the course of their husband's treatment and after care, and unmet supportive care needs are often reported. Female partners may be reluctant to share their distress with their husband in order to minimize the stress of the illness on the couple's experience; and may avoid discussing issues that create emotional tension, such as sexual concerns [14]. This lack of communication means that partners often have to deal with their distress and anxiety alone with limited opportunities for psychosocial care [18]. The distress experienced by partners is exacerbated by their husbands' reliance on them for emotional support, with partners having to manage not only their own anxiety, but also the distress of their husbands [14].

Protecting one's partner from emotional distress may have significant costs to one's own well being and diminish relationship quality over time [19]. Patients' and partners' abilities to cope with prostate cancer and subsequent treatment side-effects are interrelated [20] and can negatively impact on the marital relationship [21]. The reactions of partners to sexual dysfunction and the support they provide appears to affect the level of acceptance of sexual changes experienced by men [22]. As well, the female partner's ability to still enjoy sex without major dysfunction is a strong predictor of better sexual satisfaction in the male partner [10]. The disparate needs of couples experiencing sexual dysfunction highlights the need to provide couples with targeted support that promotes communication and adjustment to sexual outcomes. In work with couples in which the woman had breast or gynecological cancer, enhancing couple communication and conjoint coping with cancer treatments significantly enhanced women's sexual satisfaction [23]. Moreover, this couple focused approach increased couple discussion of cancer related issues, and reduced the unhelpful tendency of some people to avoid discussion. In a similar manner, it is proposed that attending to the couple relationship, promoting a sense of conjoint coping and addressing sexual needs within the relationship, will enhance both partners' adjustment to prostate cancer and increase the chance of adherence and better sexual outcomes including erectile function.

### Approaches to Intervention Delivery

By contrast to women, men are less likely to seek help for psychological distress; are under-represented as clients to cancer support services; are reluctant to utilise effective sexual aids after prostate cancer treatment *despite *high levels of dissatisfaction with the sexual outcomes of treatment. Effective support interventions need to utilise delivery methods and sources that are acceptable to this patient group. Men and their partners prefer individual consultations for sexuality support after prostate cancer [16]. Tele-delivered interventions are highly acceptable to this group, and web/computer based programs are frequently accessed by men for medical and procedural information [24,25]. Remote access delivery methods overcome geographical barriers to access and so are applicable to geographically dispersed populations with high potential for population-based translation.

A source of support that has high uptake amongst men with prostate cancer in Australia and internationally is peer support, with men reporting that peer discussions provide informational and emotional support and reduce feelings of social isolation [26]. A feasibility study of a dyadic peer support program for men with prostate cancer reported reduced depression and improved self efficacy in the short term, with men most frequently discussing incontinence, erectile dysfunction and Prostate-Specific Antigen testing with their matched peers [27]. As well, a randomised controlled trial of a group education program to assist men to adjust to prostate cancer treatments [28] found that only by adding peer discussion to the provision of information by an expert was sexual bother alleviated significantly, relative to a control group. An advantage of peer support that is provided by veteran patients is that it is inexpensive by comparison to professionally delivered approaches, such as specialist nurses. While this approach is highly promising, to date randomised controlled trials to assess the effectiveness of peer support in improving men's adjustment have not been undertaken. However, based on research to date a peer delivered counselling intervention paired with education may have equal efficacy to health professional delivery. As well, the relative cost savings for a peer support approach as compared to professional approaches, although not yet quantified, make this a potentially cost effective source of support.

### Intervention Studies Targeting Sexuality

To date intervention research targeting sexuality after prostate cancer is scant. Two trials noted improvements in sexual satisfaction, but not functioning, following general psycho-educational interventions [24,28]. These studies were limited by not including the man's partner [24,28]; not targeting men early in the cancer treatment continuum [28]; and not controlling for type of cancer treatment [24,28]. One of the only intervention studies to focus specifically on improving sexual function was a randomized trial comparing four face-to-face couple counselling sessions to similar sessions for the man alone, with the female partner just reading educational material and collaborating with homework tasks [17]. Men and their partners in both conditions reported improved sexual function and satisfaction at three month follow up and increased utilisation of medical treatments for ED at three and six months; gains in sexual function diminished at six months. Study limitations included low statistical power from a small sample size and that as men were an average of 27 to 30 months post-treatment at baseline, the critical opportunity for early intervention was missed. As well, face-to-face delivery method is relatively expensive, hard to access, and difficult to translate into a population-based cost-effective approach.

We propose that greater attention to the couple relationship in the intervention would improve female sexual or couple relationship satisfaction. Moreover, given the strong association between sexual and relationship satisfaction, particularly for women [29], enhancing the couple relationship is likely to improve long-term maintenance of sexual satisfaction improvements.

## Methods/Design

### Study Aims and Hypotheses

The overall study aim is to compare the efficacy of peer-delivered telephone support with DVD educational resource, vs. oncology nurse-delivered telephone counselling with DVD educational resource, vs. usual care in improving both men's and women's sexual and psychosocial adjustment at 3, 6 and 12 months after treatment for localised prostate cancer. In doing so we will also compare the cost-effectiveness of support by trained peers vs. nurse counsellors; and identify demographic, medical and psychosocial variables that predict improvement in psychosexual adjustment in prostate cancer patients and their partners with each intervention approach.

The intervention will utilise a cognitive behavioural approach that has been found to be effective in promoting positive adjustment after cancer [30], along with couple relationship education focussed on relationship enhancement and helping the couple to conjointly manage the stresses of cancer diagnosis and treatment [19]. The study will have three arms: (1) usual care (2) telephone support by a trained male peer support volunteer who is a prostate cancer survivor with DVD education and (3) oncology nurse-delivered telephone counselling with DVD education.

It is hypothesised that 3, 6, and 12 months after surgery for localised prostate cancer:

1. By contrast to couples in usual care, couples who receive either the peer or nurse delivered intervention will have a more positive sexual adjustment; lower unmet sexuality supportive care needs; more positive attitudes to sexual help seeking; higher uptake of erectile aids; improved psychological adjustment and quality of life.

2. Couples who receive the peer and nurse delivered intervention will have similar sexual adjustment; sexuality supportive care needs; attitudes to sexual help seeking; uptake of erectile aids; psychological adjustment and quality of life.

3. The peer delivered intervention will be more cost effective by comparison to the nurse delivered intervention.

### Intervention

Usual care will consist of the man's standard medical management and existing written educational materials. For the two intervention arms, the eight sessions of phone support/counselling will include enhanced couple communication and conjoint coping content and material relevant to the early treatment phase. An audiovisual DVD resource with Tip Sheets will accompany the intervention to enhance the psycho-education and sexuality education components and to also provide actor role models for effective couple communication about sexuality and intimacy. The nurse counselling sessions will follow principles of cognitive-behavioural sex and marital therapy and will utilise an adult learning approach in which partners' self-select goals to focus on while working through the program. Content includes education about prostate cancer, menopause, and sexuality; assigned behavioural homework including increasing expression of affection and non-demanding sexual touch; challenging negative beliefs about prostate cancer, aging, and sexuality; and helping the couple choose a medical treatment for ED that is acceptable to both partners, and integrating this into their sexual relationship. Additional components that target the challenges of the early treatment phase (e.g., urinary incontinence, pain, sleep disturbance, psychological distress) will be additionally selected by the couple if relevant.

Peer support is based on the support partner or 'veteran' patient having personal experience and knowledge about the cancer experience; a unique personal insight into effective ways to cope; and the ability to form a support relationship that is derived from the connection of shared experience. In this way peer support can reduce feelings of isolation and stigma (the sense of being the 'only one'); can convey emotional, social, informational and practical support; and through role modelling can communicate realistic hope and optimism about the future. Peer support volunteers will be prostate cancer survivors who are at least 12 months post treatment and who have support group experience. The intervention will follow the same couples-based approach as the nurse counselling intervention but will be oriented to empathic mutual support and education rather than in depth sex and marital therapy.

The patient's partner will be invited to participate in all phone sessions, and actual participation will be recorded by the peer/therapist for each phone session, as well as minutes of counselling time, for inclusion in analyses. Support/counselling calls are timed to correspond with the challenges associated with preparing for and recovering from radical prostatectomy. The first two calls will occur prior to surgery; four fortnightly calls (Sessions 3 to 6) are timed to commence two weeks after surgery; a further two calls (Session 7 to 8) 16 and 22 weeks post-surgery.

### Participants

With the strong endorsement and support of Queensland Urologists, patients will be referred to the project from private urology practices and public hospital outpatient clinics in Queensland, Australia. Informed written consent will be obtained by study trained research nurses who will contact potential participants after referral to the study. We will recruit 70 couples per condition over a 12 month period (allowing for 10% attrition from treatment; 210 couples in total to be recruited). Assuming a moderate effect size of d = 0.5, alpha at .05, the resulting power with 70 couples per condition is 0.8. Inclusion criteria are that the men must: (1) have been newly diagnosed with localised prostate cancer and have chosen radical prostatectomy as their treatment approach (2) be currently in a heterosexual cohabitating couple relationship (3) be able to read and speak English (4) have no previous history of head injury, dementia or psychiatric illness (5) have no other concurrent cancer. As the intervention has been developed based on previous data for heterosexual couples this intervention is unlikely to be helpful for homosexual couples.

### Study Integrity

Ethical approval has been obtained from the Griffith University Human Research Ethics Committee. The study design will be guided by the CONSORT statement [31]. Randomisation to study condition will occur following the completion of baseline assessment. Assessments will be by self-report pen and paper measures and project staff tracking assessments will be blinded to condition. Randomisation will occur in blocks of 12, with each condition randomly generated 4 times within each block to ensure an unpredictable allocation sequence with equal numbers of couples in each group at the completion of each block. This sequence will be undertaken by the project manager and concealed from investigators. Therapy will be manualised and all intervention calls audiotaped with 25% reviewed to ensure treatment adherence. All analyses will be conducted on the basis of intention to treat.

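### One fixed, published block size of 12 makes the end of each block deducible in the worst case, and concealment is stated for investigators but not for the nurses who recruit

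*Protocol article*

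**What the plan says.** Under Study Integrity, the protocol article describes the allocation as follows: "Randomisation will occur in blocks of 12, with each condition randomly generated 4 times within each block to ensure an unpredictable allocation sequence". The sentence goes on to give a second purpose, balance: "with equal numbers of couples in each group at the completion of each block". On custody it says: "This sequence will be undertaken by the project manager and concealed from investigators". On timing: "Randomisation to study condition will occur following the completion of baseline assessment". On blinding, it says that "project staff tracking assessments will be blinded to condition".

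Under Participants, recruitment is given to a different group: "Informed written consent will be obtained by study trained research nurses who will contact potential participants after referral to the study". The target is 210 couples, 70 per condition, over 12 months.

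The arms are usual care, telephone support from a peer, and telephone counselling from an oncology nurse (Study Aims and Hypotheses). A couple and its counsellor therefore know the assignment. No stratification or blocking by site is described, so the text reads as one central sequence.

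**The concern.** The sentence puts the block structure forward as what secures unpredictability. The random order within the block does that. The forced equality at the end of each block works against it, because each completed place narrows what can follow and the twelfth place is fixed by the other eleven. With one block size, printed in the article, the structure is known to any reader.

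The arms cannot be disguised, so earlier assignments can become known among people working on the study. The people best placed to influence who enters, and when, are the research nurses who contact and consent couples, and the concealment sentence does not name them. The project manager prepares the sequence and so knows it. No separation of that role from recruitment is stated.

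The comparability of the arms at entry is at stake. A recruiter who could anticipate the next assignment might time an approach or a consent. The clinical outcomes are self-reported by couples who know their arm, so they offer little independent check on a selection effect.

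**Working it through.** **Inputs.** Blocks of 12 with 4 places per arm, and exact balance at block end (Study Integrity); 210 couples over 12 months (Participants); three visibly different arms (Study Aims and Hypotheses). The article gives no figure for predictability. Assumption for the worst case: the guesser knows the block size, where each block starts and every earlier allocation.

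**The plan's own figure.** The only computed figure is power of 0.8 at d = 0.5 and alpha 0.05. Taking alpha as two-sided (sidedness is not stated), n = 2(1.96 + 0.84)²/0.5² gives 63 per arm, and 63/(1 − 0.10) = 70. Power at 63 per arm is 0.801. The figure is reproduced, and nothing below depends on it.

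**Possible orders in a block.** 12!/(4!)³ = 34,650. Without knowledge of earlier allocations, each arm has chance 1/3.

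**Certain allocations.** A place is certain when all remaining places belong to one arm, so the number of certain places equals the length of the final run of identical assignments. By symmetry its mean is

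1 + 3/11 + (3·2)/(11·10) + (3·2·1)/(11·10·9) = 1 + 0.273 + 0.055 + 0.006 = 1.333 per block,

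or 1.333/12 = 11.1%. Two arms must be used up first (8 places), so no place before the ninth can be certain.

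**Over the whole trial.** 210/12 = 17.5, which is 17 full blocks plus 6 places. The half block contributes no certain places: 17 × 1.333 = 22.7, and 22.7/210 = 10.8%, or about 23 couples.

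**Best guess.** The guesser always picks the arm with most places left. Exact recursion over the block gives 6.14 correct of 12, or 51.2%, against 33.3% by chance. Over 210 couples, with the half block included, the figure is 50.9%. In a full block, at least one arm is already excluded for 3.47 of 12 places (28.9%).

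**Pace.** 210/12 months = 17.5 couples a month, so a block of 12 fills in about 12/17.5 = 0.69 months, roughly three weeks.

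**Alternatives.** The rows for varying sizes assume equally likely sizes and a guesser who knows the set of sizes and all past allocations, but not the size of the current block (simulation of 210 couples).

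| Scheme | Best guess correct | Certain |
|---|---|---|
| Fixed 6 | 56.1% | 20.0% |
| Fixed 9 | 53.2% | 14.3% |
| Fixed 12 (plan; full blocks) | 51.2% | 11.1% |
| Fixed 15 | 49.7% | 9.1% |
| Varying 3, 6, 9, 12 | about 54% | about 2% |
| Varying 9, 12, 15 | about 51% | about 2% |
| Varying 12, 15, 18 | about 49% | about 2% |

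Varying the size removes most of the certainty. It lowers best-guess accuracy only if the average block is also larger than 12. A mix weighted to small blocks raises it.

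**The case against.** The case for the plan is substantial. Twelve is a fairly large block for three arms, and the full sentence assigns balance as well as unpredictability to the scheme, so its wording is ordinary. The worst case needs knowledge that the article attributes to no recruiter. The oncology nurses who deliver counselling are not said to be the research nurses who obtain consent, and a counsellor who knows their own couples does not see the sequence across three arms. Staff who track assessments are blinded. Randomisation follows the baseline assessment, and the measures are administered by mail, so a couple's place in the sequence depends partly on when they complete it. Two calls must precede surgery, which limits any delay. The concealment mechanism is detail that an article may leave to the full protocol.

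Most of this stands, and it rules out two stronger readings. A reader might infer that the sequence is open to the nurses, or that allocation is predictable in practice. The article is silent on what the nurses know; it does not say that concealment is limited to investigators. A reader might also infer that selection bias could never be detected. Baseline data precede randomisation, so imbalance on measured variables can be examined and adjusted for; only unmeasured imbalance would stay hidden. Nor is every outcome self-reported: service use and costs come from Medicare records.

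The objection does not remove the stated choices themselves: a single published block size, the project manager as the source of the sequence, and a concealment sentence that names a group other than the one that recruits. Randomising after baseline prevents steering once a couple is randomised, but it does not stop someone who anticipates the next arm from acting before consent.

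**Conclusion.** The point holds as a cheap improvement to stated choices, of minor to moderate severity. It does not show that concealment has failed. With full knowledge of block start and past allocations, about 11% of allocations (about 23 of 210) are certain and about 51% can be guessed, against 33% by chance. These are upper bounds that rest on one central sequence and complete tracking. With no knowledge of past allocations, predictability is no better than chance. The stated rationale should credit random order with unpredictability and blocking with balance. The concealment statement should cover the staff who contact and consent couples. Power and sample size are unaffected.

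**What to change.** 1. Use computer-generated blocks of randomly varying size, undisclosed to study staff and averaging no less than 12. Sizes 9, 12 and 15 give about 51% best-guess accuracy and 2% certain allocations; sizes 12, 15 and 18 give about 49% and 2%. Avoid a mix such as 3, 6, 9 and 12, which raises best-guess accuracy to about 54%.
2. Have the list generated and held by an existing team member with no part in recruitment or participant contact.
3. State that the sequence is concealed from the research nurses and other recruiting staff as well as from investigators.
4. Reword the rationale: random order for unpredictability, blocking for balance.

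The cost is a changed randomisation script, a change of custody and two sentences. The downside is slightly looser balance. Within a block, two arms can differ by at most the places per arm, which is 4 for a block of 12, 5 for 15 and 6 for 18. The present scheme does not guarantee exactly 70 per arm either, since 210 ends halfway through a block.
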